***Psychosocial functioning and mood***					
Recovery of Quality of Life-20 (ReQoL-20)		X		X	X
Visual Analogue Scale (VAS) for mood (happy, sad, anxious)			X		
Global rating of change (GRC): 1 item				X	
***Feasibility measures***					
Credibility/Expectancy Questionnaire (CEQ)		X		X	
Exit Questionnaire					X

^a^Arrow indicates continuous delivery of the assigned condition

^b^C/bal stands for counterbalancing, which was used alternate item content across multiple timepoints to prevent order effects. The specific counterbalancing schedule is available upon request

^c^The interim (i.e. weekly) assessments are completed only after completing the intervention/control session of that week

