	**Screening (-T**_**1**_** to T**_**0**_**)**	**Baseline (T**_**0**_**)**	**Interim assessments (T**_**i1-5)**_^**c**^	**6-week follow-up assessment **(**T**_**1**_**)**	**12-week follow-up (T**_**2**_**)**
Enrolment					
* Informed consent procedures*					
Participant information sheet	X				
Consent form	X				
*Eligibility check*					
Inclusion/exclusion criteria checklist	X				
Capacity assessment tool (if applicable)	X				
M.I.N.I. screening tool	X				
Beck depression inventory–II (BDI-II)	X	X		X	X
Intervention/comparator					
CURED (intervention)					
Neutral CBM-I (control)					
Assessment instruments					
*Sociodemographic information*					
Socio-demographic questionnaire		X			
*Clinical symptoms*					
M.I.N.I. MDD module		X			
Patient Health Questionnaire-9 (PHQ-9)		X	X	X	X
Beck Depression Inventory-II (BDI-II)		X		X	X
Depression, Anxiety, and Stress Scale-21 (DASS-21)		X		X	X
Generalized Anxiety Disorder-7 (GAD-7)				X	X
*Interpretation bias*					
Scrambled Sentence Task (SST)		X C/bal^b^	X C/bal	X C/bal	X C/bal
Similarity Rating Test (SRT)		X C/bal		X C/bal	X C/bal
*Cognitive content*					
Automatic Thought Questionnaire-Revised (ATQ-R)		X		X	X
Cognitive Distortions Scale (CDS)		X		X	X
*Prospective Imagery Task (PIT)*		X		X	X
*Cognitive process*					
Repetitive Thinking Questionnaire (RTQ-10)		X		X	X
Interpretation Inflexibility Task (IIT)		X		X	

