##### Target mechanism (interpretation bias) measures

**Scrambled sentences test (SST **[23, 24]**)**

A 12-item cognitive task involving rearrangement of six-word scrambled sentences into grammatically correct statements while under time pressure.

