**Similarity Rating Test (SRT **[12]**)**

A validated measure of interpretation bias in which participants read ten ambiguous scenarios followed by sentences reflecting positive and negative interpretations, rating each for similarity to the original passage.

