### Secondary outcomes

Secondary outcomes will be assessed as candidate primary outcomes and used in providing effect size estimates for power calculations for future trials.Suitability of the candidate primary outcomes will be defined by:Acceptability (feedback on burden and clarity from exit questionnaires),Variability (sufficient spread in scores without floor/ceiling effects),Sensitivity to change, defined as evidence of within-group and between-group score changes over time in the expected direction (mean change scores with 95% CIs).Descriptive statistics will be aggregated by assigned condition and presented in tables, including means, medians, standard deviations, variances, range, 95% confidence intervals and levels of missingness.

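### SST and SRT use alternating item sets but are summarised by arm only, so set differences, if there are any, enter the change-score variance or the within-arm change

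*Protocol article*

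**What the plan says.** In Table 2, SST and SRT are the only measures marked for counterbalancing. SST is marked at baseline, the five interim assessments, 6 weeks and 12 weeks, which makes eight occasions. SRT is marked at baseline, 6 weeks and 12 weeks, which makes three. Footnote b explains the mark: "C/bal stands for counterbalancing, which was used alternate item content across multiple timepoints to prevent order effects". It adds: "The specific counterbalancing schedule is available upon request". Both instruments are short. SST is described as "A 12-item cognitive task involving rearrangement of six-word scrambled sentences", and in SRT "participants read ten ambiguous scenarios".

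Both are secondary outcomes, and the article treats secondary outcomes as candidate primary outcomes for the definitive trial. Under Statistical methods {27a}, Secondary outcomes, "Descriptive statistics will be aggregated by assigned condition and presented in tables, including means, medians, standard deviations, variances, range, 95% confidence intervals". The same section defines sensitivity to change by within-group and between-group mean change scores with 95% confidence intervals. Item set and sequence are not mentioned in {27a} to {27d}, and neither is a stratification factor in {21b}. Section {5} says that the statistical analysis plan is integrated in {27a–d} and that no standalone plan will be published.

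**The concern.** Item set is a known feature of the design, and the stated analysis does not use it. What follows depends on the schedule.

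- **Sequence varies between participants.** A difference in mean score between sets adds to one person's change and subtracts from another's. It averages out of the arm mean when the sequences are balanced, but it stays in the SD of change.
- **Everyone follows one sequence.** The SD of change is unaffected, but every change between occasions that use different sets contains the set difference. Change within an arm then cannot be separated from a change of item content.

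Variance estimates are a stated objective in {10}. Effect sizes with intervals are meant to inform sample size, and change in the expected direction is one of the criteria for choosing an outcome. SST and SRT are also the two measures of the mechanism that the intervention targets.

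**Working it through.** The plan has no power figure to reproduce. Section {19} sets 30 per arm (2 × 30 = 60) from general recommendations and states no SD, effect size, alpha or power.

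**Inputs.** From the article: 30 per arm, and the occasions in Table 2. Assumed, because the article does not give them: score SD 1; correlation r between two occasions; two item sets whose means differ by d SD; half of each arm on sequence AB and half on BA.

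**Formulas.**
- Variance of change = 2(1 − r) + d², against 2(1 − r) when the sets are equivalent.
- Variance at one timepoint = 1 + d²/4, against 1.
- Implied sample size is proportional to the variance.
- Half-width of the 95% interval for the difference in change between arms = 1.96 × SD × √(2/30).

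**Results at r = 0.6**, where 2(1 − r) = 0.8:

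| d | Variance of change | SD of change | Implied n | Half-width | Single-timepoint SD |
|---|---|---|---|---|---|
| 0 | 0.80 | 0.894 | reference | 0.453 | reference |
| 0.2 | 0.84 | 0.917 | +5.0% | 0.464 | +0.5% |
| 0.3 | 0.89 | 0.943 | +11.3% | 0.477 | +1.1% |
| 0.5 | 1.05 | 1.025 | +31.3% | 0.519 | +3.1% |

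**Range over r.** For the same three values of d, implied n rises by 3.3%, 7.5% and 20.8% at r = 0.4, and by 10.0%, 22.5% and 62.5% at r = 0.8.

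**Illustration.** Take an assumed target difference of 0.4 SD, two-sided alpha 0.05 and power 0.90. At r = 0.6, n per arm based on change scores goes from 106 to 111, 117 and 138. Based on final scores it goes from 132 to at most 140.

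**Simulation** (20,000 trials per setting, 30 per arm, r = 0.6, d = 0.5):

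| Schedule | Mean SD of change | Reported SE of arm difference | Actual SE | Shift in within-arm mean change |
|---|---|---|---|---|
| AB/BA balanced within arm | 1.024 | 0.264 | 0.232 | about 0 |
| AB/BA assigned at random | 1.020 | 0.263 | 0.263 | about 0 |
| One sequence for all | 0.891 | 0.230 | 0.229 | 0.500 |
| Same set on both occasions | 0.891 | 0.230 | 0.230 | about 0 |

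With equivalent sets, or with the set effect removed, the SE is 0.894 × √(2/30) = 0.231.

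**Which contrasts cross sets.** Under strict alternation of two sets, SRT runs A-B-A. Baseline to 12 weeks then uses one set, and baseline to 6 weeks crosses. For SST, baseline is occasion 1, 6 weeks is occasion 7 and 12 weeks is occasion 8. Baseline to 6 weeks then uses one set, and baseline to 12 weeks crosses. Each measure would keep one crossing contrast among its two main ones. Other schedules would give other patterns.

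**The case against.** The strongest objection is that the effect is conditional on things the article does not state. It does not say that the sets differ, how many there are, or whether the sequence varies between people. The schedule exists and can be requested, and the full protocol (version 1.2) is not shown. With equivalent sets nothing happens. This stands, and it is why the point is put as a possibility. It does not remove the point: {5} places the analysis plan in {27a–d}, and a schedule held elsewhere does not alter summaries that are defined by arm alone.

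A reader might go further and infer three things that the documents do not support.

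- **That the reported intervals are wrong.** If sequences fall at random, the reported SE of 0.263 equals the actual SE, and a chance imbalance is ordinary sampling error that the interval covers. If the next trial used the same sets unadjusted, the larger SD would be the right one for planning. Only with balanced sequences does the reported SE overstate the actual one, and that error is conservative.
- **That SST and SRT are put at an unfair disadvantage against BDI-II or PHQ-9.** Section {27a} judges candidates on acceptability, spread without floor or ceiling effects, and change in the expected direction. It sets no ranking on precision.
- **That sequence should have been balanced within each arm.** Baseline assessment precedes randomisation, sequence is not a stratification factor, and Trial status reports participants already randomised. Equal numbers cannot now be guaranteed.

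It is also fair to say that the trial confines itself to description and estimation, and that nothing in {27a} forbids an adjustment. A set-adjusted estimate is still estimation, so it fits that limit.

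**Conclusion.** The point holds in conditional form. SST and SRT alternate item content, and the stated summaries ignore it. If the sets differ and sequences vary between participants, change scores that cross sets carry removable variance worth about 5%, 11% or 31% of implied sample size at r = 0.6 and d = 0.2, 0.3 or 0.5. The values of r and d are assumptions. The effect becomes material at about d = 0.3 and above, is at most about 3% on single-timepoint SDs for d up to 0.5, and is absent from same-set contrasts. It is a loss of efficiency that errs towards a larger next trial, not a bias. If instead one sequence is used for everyone, no variance is inflated and the set shift cancels between arms, but within-arm change across different sets cannot be read as sensitivity to change. No other outcome is affected.

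**What to change.** Add the following to {27a}, Secondary outcomes:

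1. Tabulate SST and SRT baseline means by item set. Where baseline sets vary between participants, this shows whether the sets differ, which the definitive trial also needs to know.
2. Where sequences vary between participants, also report SST and SRT change and the between-arm difference from a linear model that includes item set or sequence. Give its residual SD beside the raw SD.
3. Where one fixed sequence is used, do not count within-arm change across different sets as evidence of sensitivity to change. Rely on the between-arm difference, or on occasions that share a set.

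The cost is one or two degrees of freedom per outcome (two or three sequences) and a few table rows. No new data are needed as long as the set given on each occasion can be recovered from the schedule. Randomisation and the conduct of the trial do not change.

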## Methods: participants, interventions, and outcomes

### Trial setting {13}

The study is conducted by the Institute of Psychiatry, Psychology & Neuroscience (IoPPN), King’s College London, co-sponsored by South London and Maudsley NHS Trust. Assessments are delivered as online questionnaires (Qualtrics links) via email, and intervention or control booklets are posted weekly to participants, who return them in one batch at the end of the 6-week period in a pre-paid envelope. Participants are asked to complete a screening call, baseline interview, and subsequently their assigned intervention and associated assessments in a private setting, without distractions where possible.

### Characteristics of the people who are needed for the trial

#### Eligibility criteria for participants {14a}

The inclusion criteria are the following:Having mild depression or above, assessed by:Scoring ≥ 15 (mild) on Beck Depression Inventory-II (BDI-II) [18] ANDAnswering “yes” to either or both of two depression questions (Section A, questions 1 and 2) in the Mini-International Neuropsychiatric Interview Screen (M.I.N.I.; [19]).Age 18 years or over.

The exclusion criteria are the following:Any medical condition that impedes the completion of the study tasks (e.g. advanced cancer, serious heart disease, stroke, dementia);Having received psychological therapy targeting the same cognitive mechanisms as the intervention in the 2 months leading up to participation;If on psychotropic medication, having changed medication or dose within the month prior to participating in the study or expected to do so during the study;Psychosis, according to screening item of the Modified MINI Screen;Substance or alcohol misuse operationalised as ≥ 2 total score on CAGE questions Adapted to Include Drug Use (CAGE-AID; [20]);Self-reported Autism Spectrum Disorder diagnosisA previous head injury resulting in a loss of consciousness;Reporting suicidal thoughts with current intent, as assessed by BDI-II item 9 and follow-up Columbia-Suicide Severity Rating Scale (C-SSRS; [21]**)** questions 3 and 4, with exclusion if answering “yes” to question 4;Participating in any other interventional study concurrently.

### Eligibility criteria for sites and those delivering interventions {14b}

This trial will be conducted at a single site under the lead of the Chief Investigator (JY), a site investigator (KK; a clinical researcher and PhD candidate), and the Project Coordinator (CF). Recruitment and intervention delivery will be undertaken by a team comprising post-graduate research assistants (RAs), MSc students, and the clinical researcher (KK).

### Who will take informed consent? {32a}

Capacity to consent will be presumed in line with the Mental Capacity Act (2005) unless in doubt, in which case assessed by researchers during screening using a tool based on the Act to determine whether the individual can understand, retain, and communicate information about the study and their participation. Informed consent will be obtained by trained members of the recruitment team (postgraduate MSc students, graduate research assistants, and the site investigator), using secure eConsent forms sent with the participant information sheet at least 24 h in advance, and copies are stored securely on the university’s password-protected servers.

### Additional consent provisions for collection and use of participant data and biological specimens {32b}

We will include an explicit item in our informed consent procedures explaining the process for fully anonymised data sharing via the national repository, UK Data Archive. Only participants who select this option will be included in the archived dataset.

## Intervention and comparator

### Intervention and comparator description {15a}

#### Intervention condition (CURED)

The CURED intervention comprises six sessions, each containing 40 three-line scenarios presented in a booklet format. In each scenario, the ambiguity is resolved by a positive word fragment at the end of the passage, followed by a comprehension question (for a full description of the training procedure, see [12], pp. 150–151). Finally, participants generate prospective imagery related to the passage for 8 s [22]. An example intervention item is shown in Fig. 1.

#### Control condition (neutral CBM-I)

The control condition also comprises six sessions of booklets with 40 three-line scenarios in each session, employing the exact same procedural flow as the intervention. It matches the intervention in delivery, number and length of scenarios, structural format, and imagery instructions, with the sole difference being that the content focuses on emotionally neutral, everyday activities and factual descriptions (please see Fig. 2 item as an example).

**Fig. 2 Fig2:**
[figure not shown]
An example control condition item

### Criteria for discontinuing or modifying allocated intervention/comparator {15b}

Participants may discontinue or be discontinued if adverse events (AEs), serious adverse events (SAEs), or mood worsening are identified at any point during the study and deemed related to the study procedures. This is assessed using an adverse events checklist (see Harms {17} for more information).

### Strategies to improve adherence to intervention/comparator {15c}

Adherence to the allocated intervention or control condition will be supported and monitored through structured participant contact. At the first session, a researcher will conduct an orientation call to explain procedures and address any questions. Weekly email reminders will be sent to encourage ongoing engagement, with additional reminders if sessions are missed. A scheduled check-in call will take place at week 3 (mid-point) to assess mood, review progress, troubleshoot difficulties, and reinforce adherence. Researchers will also conduct calls at each main assessment point (baseline, post-intervention, and 12-week follow-up) to support participation and ensure data completeness.

### Concomitant care permitted or prohibited during the trial {15d}

Participants receiving psychotherapy involving cognitive components are eligible only after a 2-month washout period following the end of therapy. Where antidepressant or other psychotropic medication has been recently initiated or adjusted, eligibility is deferred for 1 month after medication stabilisation. During recruitment and follow-up calls, researchers emphasise that participant wellbeing is the priority and that involvement in this trial should not delay or prevent access to clinical care. Participants who initiate psychotherapy or medication change after randomisation will not be excluded from the trial.

### Ancillary and post-trial care {34}

No specific ancillary or post-trial care is necessary as part of this feasibility trial; participants will continue with their usual treatment.

### Outcomes {16}

#### Primary outcomes

As this study is a feasibility evaluation of the CURED intervention, there is no single primary clinical outcome. Instead, (1) feasibility, (2) acceptability, (3) blinding integrity, and (4) safety will be assessed across several domains. These metrics will inform progression criteria for a future definitive RCT.*Feasibility* will be quantified using response, recruitment, eligibility, and randomisation rates; adherence; retention; and weekly assessment completion rate.*Acceptability* will be assessed using quantitative measures (Credibility and Expectancy Questionnaire; Exit Questionnaire) and qualitative interviews exploring user experience, barriers, and facilitators to engagement.*Blinding integrity* will be evaluated by the success of randomisation, percentage of unblindings, and by examining whether participants and researchers can correctly guess allocation at the final 12-week follow-up (last contact point).*Safety* will be evaluated throughout the trial by monitoring and documenting adverse events (AEs) and serious adverse events (SAEs), with frequency, severity, and relatedness recorded at each assessment point.

#### Secondary outcomes

The secondary outcomes will assess the suitability of candidate clinical and cognitive measures as potential primary outcomes in a future definitive RCT. This includes evaluating their sensitivity to change over time and estimating between-group effect sizes (with 95% confidence intervals) to inform sample size calculations (please see Table 2 for the full assessment schedule).

##### Target mechanism (interpretation bias) measures

**Scrambled sentences test (SST **[23, 24]**)**

A 12-item cognitive task involving rearrangement of six-word scrambled sentences into grammatically correct statements while under time pressure.

**Similarity Rating Test (SRT **[12]**)**

A validated measure of interpretation bias in which participants read ten ambiguous scenarios followed by sentences reflecting positive and negative interpretations, rating each for similarity to the original passage.

##### Clinical symptom measures

**Mini-International Neuropsychiatric Interview (M.I.N.I. **[19]**)—MDD module**

A structured diagnostic interview used to determine whether participants meet DSM/ICD criteria for major depressive disorder at baseline.

**Beck Depression Inventory-II (BDI-II **[18]**)**

A 21-item self-report questionnaire assessing the severity of depressive symptoms on a 0–3 scale, with higher scores indicating greater depression severity.

**Patient Health Questionnaire-9 (PHQ-9 **[25, 26]**)**

A 9-item self-report scale measuring depressive symptoms on a 0–3 scale, widely used for tracking symptom severity and change over time.

**Depression, Anxiety, and Stress Scale–21 (DASS–21 **[27]**)**

A 21-item self-report measure assessing depression, anxiety, and stress, scored on a 0–3 scale to yield three subscale totals.

**Generalised Anxiety Disorder-7 (GAD-7 **[28]**)**

A 7-item self-report questionnaire evaluating anxiety severity on a 0–3 scale, with higher scores reflecting greater anxiety.

#### Exploratory measures

A set of cognitive content and process measures will be included to examine potential mechanisms of change and generate hypotheses for future work.

##### Cognitive content measures

**Automatic Thoughts Questionnaire–Revised (ATQ-R **[29]**)**

A 40-item self-report measure of automatic thoughts relevant to depression, comprising 30 negative and 10 positive items rated on a 5-point scale to yield total frequency scores of negative thinking.

**Cognitive Distortions Scale (CDS **[30]**)**

A 20-item questionnaire assessing 10 types of cognitive distortions across interpersonal and achievement domains, rated on a 7-point scale indicating how often each distortion occurs.

**Prospective Imagery Task (PIT **[31]**)**

A 20-item task assessing the vividness of positive and negative future-oriented mental imagery, with higher ratings indicating more vivid prospective imagery.

##### Cognitive process measures

**Repetitive Thinking Questionnaire (RTQ-10 **[32]**)**

A 10-item self-report scale measuring the tendency to engage in repetitive, transdiagnostic negative thinking following distressing events.

**Interpretation Inflexibility Task (IIT **[33]**)**

A picture-based paradigm assessing interpretation bias and flexibility across three progressively clarified social scenarios, with higher scores reflecting greater interpretive flexibility.

##### Psychosocial functioning and mood monitoring

**Recovering Quality of Life (ReQoL-20 **[34]**)**

A 20-item self-report measure of recovery-oriented quality of life, where higher total scores indicate better well-being and functioning.

**Visual Analogue Scales (VAS) for mood (happy, sad, anxious)**

Three single-item scales assessing momentary levels of happiness, sadness, and anxiety on a 0–100 continuum, with higher scores indicating greater intensity.

**Global Rating of Change (GRC **[35]**)**

A single-item measure of perceived overall change in health status since baseline, indicating whether participants feel worse, the same, or better.

